#### Secondary questions

Does the new approach for implementation of integrated T2DM and periodontitis care:

lead to better periodontal health in response to dentist-initiated T2DM care?improve patients’ quality of life?lead to more risk-tailored utilization of care and medication?lend itself for practice implementation as anticipated? (process evaluation)provide good value-for-money?evoke specific provider payment preferences?

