##### In dental practices

% of teeth with pocket probing depth > 4 mm and bleeding on probing (BOP) [primary data].T2DM medication (no medication, oral medication, insulin injections) [primary data].Patients’ quality of life [primary data].Utilization of T2DM care (blood sugar-parameters, inclusion in T2DM-DMP) [primary data].Utilization of periodontal care [claims data].

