##### Baseline survey (T0)

Patients in both studies receive a written questionnaire on sociodemographic data and a self-disclosure of medical conditions. The questionnaire further contains a question on current, subjective health, translated from the publicly available, validated Short Form 36 (SF-36)-questionnaire by RAND Corporation [23]. Additionally, the questionnaire contains the respective questions for periodontitis/T2DM risk assessment (in the dentist study, this is only the case for the intervention group), so patients may calculate their risk score. The medical/dental assistant will be available for questions during this process. The further course differs depending on the study and risk-score.

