##### Survey T1 (first follow-up)

The medical assistant in the general practice identifies all participating patients during a regular DMP-appointment. In the dental practice, the dental assistant identifies all participating patients during a regular appointment. Patients are asked to fill out another written questionnaire on their health and a potential periodontitis/T2DM diagnosis and therapy. Subjective health is once again assessed using the first question of the SF-36. To allow for a comparison with the patient’s subjective health at T0, question 2 of the SF-36 will be asked as well.

In the GP-study, the GP asks the patients about their potential periodontitis diagnosis and/or therapy. The primary endpoint measured during the regular DMP-appointment as well as the questionnaire data (including secondary endpoints) for T1 will be transferred to the research database by the medical assistant.

In the dentist study, the dentist in both control and intervention group asks the patients about their potential T2DM diagnosis and/or therapy. The current periodontal status and the periodontal services provided will, together with the questionnaire data, be transferred to the research database by the dental assistant.

The second, and final, follow-up survey takes place 6 to 12 months after T1, depending on when the patient was recruited for T0.

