#### Dentist study

For the primary outcome, we will test the null hypothesis H_0_^ZA^: π_IG_^T1−T0^ = π_KG_^T1−T0^ against the alternative hypothesis H_1_^ZA^: π_IG_^T1−T0^ ≠ π_KG_^T1−T0^ on a two-sided significance-level of 5%. π_IG_^T1−T0^ and π_KG_^T1−T0^ represent the rate of new diabetes diagnoses between baseline (T0) and after 12 months (T1) in both groups.

Primary analysis will be performed using a generalized, logistic mixed model adequately representing the multi-level structure of data (practice on level 1, patients on level 2). For the test of H_0_^ZA,^ the „rate of new diabetes diagnoses between T0 and T1” will be used as the dependent variable. The model contains the practice as a random effect and the group (intervention vs. control), age, sex, insurance status, state and residential area as fixed effects on the patient level.

It can be assumed that claims data will be complete and missing values will only occur in the additional study data and the questionnaires. Missing values of the primary outcome will be imputed using multiple imputation [27] while accounting for the baseline-variables age, sex, insurance status and residential area. To check for the sensitivity of results, assumptions on missing values will be analyzed and an alternative procedure to handle missing data, such as an analysis of the full dataset, will be looked into. Further sensitivity analyses include sub-group analyses for both states and for insurance status.

Secondary endpoints will be presented descriptively first. Where appropriate, secondary endpoints will be explored similar to the primary analysis. For binary endpoints, logistic regression analyses will be performed. For continuous endpoints, linear regression analyses will be performed. For all estimated effects we will present descriptive p-values and 95% confidence intervals. All analyses are performed using a validated R environment with R version 4.0.0 or higher. The primary analysis is independently counter-programmed in SAS version 9.4 or higher.

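### The secondary endpoint named quality of life does not match the only related measurement described, which is self-rated health by one or two SF-36 questions

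*Protocol article*

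**What the plan says.** Under Secondary questions, the protocol asks whether the new care approach will "improve patients’ quality of life". Under Secondary endpoints, the entry "Patients’ quality of life [primary data" appears for GP practices and again for dental practices, in both cases with primary data as its only source. Neither entry names an instrument, a score or a time point.

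The survey sections describe what patients are asked:

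- **Baseline survey (T0):** "Patients in both studies receive a written questionnaire on sociodemographic data and a self-disclosure of medical conditions". To this the section adds one health item: "The questionnaire further contains a question on current, subjective health, translated from the publicly available, validated Short Form 36 (SF-36)-questionnaire". The rest is the risk-score questions, which in the dentist study only the intervention group receives.
- **Survey T1:** "Subjective health is once again assessed using the first question of the SF-36". For comparison with T0, "question 2 of the SF-36 will be asked as well". The other content concerns health and the diagnosis and therapy of the other disease.
- **Survey T2:** the same two SF-36 questions, in general and in dental practices.

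For secondary endpoints in the dentist study the analysis section says, where appropriate: "For binary endpoints, logistic regression analyses will be performed. For continuous endpoints, linear regression analyses will be performed". The benefit-benefit analysis under Economic evaluation compares changes in subjective health between groups.

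**The concern.** The endpoint and its measurement carry different names, and the names stand for different things. The research question and the endpoint lists speak of quality of life. The survey sections and the economic evaluation speak of subjective health. No section says how one becomes the other.

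If the plan is followed as written, the answer to a question on self-rated health will be reported in the line reserved for quality of life. A difference would be read as an effect on quality of life, and no difference as its absence. The Discussion says that the study should inform a decision on adopting the model as standard care, and it counts better quality of life among the expected benefits, so the label has weight outside the statistical report.

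An analysis plan can settle scoring and models. It cannot supply questionnaire items that were never asked. The mismatch therefore lies in what the protocol states, and is not a detail that it may leave to a later document.

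**Working it through.** No arithmetic applies: the point concerns what is measured, and both sample size calculations refer to the primary endpoints. The check follows every mention of quality of life, subjective health and the SF-36 through the protocol.

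**Step 1. Where quality of life is named.** Secondary questions; Secondary endpoints for GP practices; Secondary endpoints for dental practices. It also appears as an expected benefit in the Abstract, under Expected use and insights, and in the Discussion. None of these places names an instrument.

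**Step 2. What is collected at each visit.**

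| Visit | Related items described | Count | Name used in the protocol |
|---|---|---|---|
| T0 | one SF-36 question on current health | 1 | subjective health |
| T1 | SF-36 questions 1 and 2 | 2 | subjective health |
| T2 | SF-36 questions 1 and 2 | 2 | none given beyond the question numbers |

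That the T0 item is SF-36 question 1 is an inference. The T1 section says that subjective health is assessed again with that question. Multi-item or multi-domain quality-of-life scales described at any visit: 0.

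**Step 3. What can be compared with baseline.** Question 2 is first asked at T1. The only item repeated from T0 is therefore the single question on current health.

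**Step 4. Whether a comparison group exists.**

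- *Dentist study:* both groups are recruited in practices and surveyed. Only the risk-score questions are withheld from the control group, so both groups answer the health item.
- *GP study:* the control group is calculated from claims and DMP documentation data, and the survey is described only for recruited patients. The source labels point the same way. Periodontitis therapy and T2DM medication are marked as coming from primary and claims data, quality of life from primary data alone. No control value for this endpoint is described.

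**Step 5. What the stated model adjusts for.** In the dentist study, the primary model has practice as random effect, and group, age, sex, insurance status, state and residential area as fixed effects. Exploring the health item in a similar way would leave out its own T0 value, although that value is collected.

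**The case against.** The strongest reply is that the link between endpoint and items is inferred. No sentence equates quality of life with the SF-36 questions. The T1 and T2 sections mention a written questionnaire on health without listing all of it, and the article condenses a fuller protocol. A further instrument cannot be excluded. This stands, and the fix allows for it. The inference is nevertheless strong: the T0 content is itemised, the SF-36 questions are given by number for the follow-up visits, and nothing else that could serve appears.

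Several stronger readings are tempting, and the protocol does not support them:

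- A reader might infer that quality of life is not measured at all and the question cannot be answered. That goes too far, because self-rated general health is a crude indicator of one aspect of health-related quality of life.
- A reader might infer that the protocol claims validation for the single item, or that the study team made its own translation. The text calls the SF-36 questionnaire validated and says that the question was translated, but not by whom or how.
- A reader might take the share of SF-36 questions used as the size of the problem. Items are not equal parts of a construct, so such a share measures neither bias nor lost information.
- A reader might infer that the analysis is wrong because only binary and continuous endpoints are covered. The response format is not printed, the secondary analyses are exploratory, and a suitable model can be set in the analysis plan.
- A reader might take the statements on better quality of life in the Abstract and Discussion as conclusions planned from this item. They read as rationale and expectation.

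It is also fair that the benefit-benefit analysis already uses the accurate name. That supports using the same name for the endpoint.

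**Conclusion.** The point holds as a mismatch between a named endpoint and its described measurement. As the protocol stands, the data would support a statement on self-rated general health. They would not support a general statement on quality of life, whichever way the result falls.

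Its reach is one secondary question and one secondary endpoint in each of the two studies. Primary endpoints, sample sizes and confirmatory tests are unaffected. The change should be made, because it alters what the trial may conclude on this question and costs almost nothing.

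The conclusion rests on two assumptions: that the full questionnaire contains no other quality-of-life instrument, and that the T0 item is SF-36 question 1. If the first is wrong, naming the instrument resolves the point.

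**What to change.** 1. In Secondary questions and in both Secondary endpoints lists, replace quality of life by self-rated general health (SF-36 question 1, with question 2 as the change item at T1 and T2), and limit the conclusion to that. If the full questionnaire contains a quality-of-life instrument, name it as the endpoint measure instead.
2. In the dentist study, compare the groups on question 1 with a mixed model: practice as random effect, group, the covariates of the primary model and the T0 response. The model should suit the response scale, for example an ordinal model if the answers are ordered categories. Adjusting for the T0 response should gain precision and needs no extra data collection.
3. In the GP study, report the item for the intervention group only and make no between-group comparison on it.

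The cost is an edit of the wording and one model specification, with no new items or visits. The downside is a narrower secondary claim than the one the protocol now announces.

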## Evaluation approach

### Impact evaluation

#### Study in general practices and dental practices

The GP study is a practice-based, multi-center, non-randomized, controlled trial. The intervention group will be recruited in general practices, the control group will be calculated from insurer claims data as well as from DMP documentation data across insurers (triangulation in comparison to the insurer-data) parallel to the clinical intervention group.

The dentist study is a practice-based, multi-center, cluster-randomized, controlled trial with a control and an intervention group. Both groups are recruited in dental practices. Patients are clustered in practices, hence a randomization on cluster-level was deemed appropriate.

Both studies will be carried out in the German states of Baden-Württemberg and North Rhine-Westphalia.

##### Inclusion & exclusion criteria

Table 1 illustrates inclusion & exclusion criteria for practice personnel and patients alike in the main study.

**Table 1 Tab1:** Inclusion and exclusion criteria of the main study

	Practice & practice personnel	Patients
**Inclusion criteria**	- Legal age - Ability to consent	
	- Established, licensed physicians and assistants - Based in Baden-Wuerttemberg or North Rhine-Westphalia - Working computer system with internet connection - Patients physically visit the practice	- Insured with a statutory health insurer - GP-study: In T2DM-DMP in 4 of 5 past quarters - Dentist study: Need for systemic periodontitis therapy
**Exclusion criteria**	Persons who : - Live in a nursing home - Have a legal guardian - Are not of legal age - Are cognitively or linguistically incapable to participate	
	- Are not licensed as physician - Don’t practice in Baden-Württemberg or North Rhine-Westphalia	- Are not insured with a German statutory health insurer (or not entitled to care that exceeds basic health care coverage) - GP-study: a periodontitis therapy in the past 12 months - Not in the T2DM-DMP in 4 of 5 past quarters - Dentist study: Previously diagnosed with diabetes

##### Randomization procedure

###### General practitioner study

To ensure comparability of the (calculated) control group and the (recruited) intervention group, triangulation will be performed using insurer claims data and DMP-documentation data across insurers (pseudonymized data on person-level). Consent will be obtained from the Federal Office for Social Security in Germany to acquire and use the data without needing informed consent from each patient.

Contrary to insurer claims data, DMP data lacks information on secondary endpoints. However, representativeness of DMP data that has been gathered across all insurers is higher than that of data from a single insurer. Triangulation can improve validity of control group data and its comparability to the intervention group (in the sense of an emulated counterfactual with demographic characteristics of the intervention group). For intervention patients, there will be survey data equal to the claims data as well as additional survey data.

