## Materials & methods

### Endpoints

#### Primary endpoints

##### In general practitioner (GP) practices

HbA1c reduction among patients in the T2DM Disease Management Program (T2DM-DMP) who had not received periodontitis therapy within the past 12 months. Recorded by medical assistants at: T0 (recruitment); T1 (after 12 months); T2 (after max. 24 months). [primary data]

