#### Secondary endpoints

##### In GP practices

Utilization of periodontitis therapy (yes/no) [primary & claims data].T2DM medication (no medication, oral medication, insulin injections) [primary & claims data].Patients’ quality of life [primary data].

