### Statistical hypotheses and analyses

#### General practitioner study

For the primary outcome, we will test the null hypothesis H_0_^HA^: µ_IG_^T1−T0^ = µ_KG_^T1−T0^ against the alternative hypothesis H_1_^HA^: µ_IG_^T1−T0^ ≠ µ_KG_^T1−T0^ on a two-sided significance-level of 5%. µ_IG_^T1−T0^ and µ_KG_^T1−T0^ represent the reduction of the HbA1c-parameter between baseline (T0) and after 4 quarters (T1) in both groups.

Evaluation of the intervention contains descriptive and explorative statistical analyses of gathered study data as well as available claims data. The goal is an independent, scientifically valid and differentiated statement on effectiveness of the intervention regarding a reduction of the HbA1c parameter using an intervention study with parallel control group. The control group will be calculated from insurer claims data as well as DMP-documentation data across insurers. Using their registration number, intervention practices will be removed from the control group data. Study data will be described using descriptive methods.

Primary analysis will be a hierarchical, linear mixed model representing the multi-level structure of the data (level 1: practice, level 2: patient). For the test of H_0_^HA^, the dependent variable will be “reduction of HbA1c between T0 and T1”. The model contains the practice as a random effect and HbA1c at baseline (T0), age, sex, insurance status, state and residential area as fixed effects on the patient level. Here, only variables that are also included in claims data can be used.

It can be assumed that claims data will be complete and missing values will only occur in the additional study data and the questionnaires. Missing values of the primary outcome will be imputed using multiple imputation [27] while accounting for the baseline-variables age, sex, insurance status and residential area. Assumptions on missing values will be analyzed and an alternative procedure to handle missing data, such as an analysis of the full dataset, will be looked into.

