#### Economic evaluation

A cost-cost-analysis will compare total costs for periodontitis- and diabetes-specific treatments in the intervention group with a representative control group. Simultaneously, a corresponding benefit-benefit-analysis will, in the context of a difference-in-differences analysis, analyze subjective health changes of study participants over the course of the study between intervention and control group.

In case of a positive or inconclusive result of these first analyses on the advantages of the intervention, the incremental cost-effectiveness-relation (ICER) of the intervention will be calculated in comparison to usual care and based on DMP and claims data as well as results from the main and process evaluation. Furthermore, there will be calculations on costs and effects of the transfer of the intervention to usual care. To calculate the ICER, differences in the costs will be compared with differences in health effects. Costs of usual care will be calculated from claims data [10]. Additional costs caused by the intervention will be estimated on the base of documented costs from the study and approximated personnel costs from the results of the process evaluation (time spent for the intervention multiplied with usual rates for personnel costs). All analyses will be performed using a validated R-environment with R version 4.2.2. or higher.

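### The protocol leaves open whether DMP records feed the control group of the GP primary test, and DMP-derived controls cannot be screened for the 12-month periodontitis-therapy exclusion

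*Protocol article*

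**What the plan says.** **Eligibility.** Primary endpoints, GP practices, defines the outcome as "HbA1c reduction among patients in the T2DM Disease Management Program (T2DM-DMP) who had not received periodontitis therapy within the past 12 months". Table 1 repeats the rule as an exclusion: "GP-study: a periodontitis therapy in the past 12 months".

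**Where therapy is recorded.** Secondary endpoints, GP practices, lists "Utilization of periodontitis therapy (yes/no) [primary & claims data" with no mention of DMP data. Randomization procedure, General practitioner study, adds: "Contrary to insurer claims data, DMP data lacks information on secondary endpoints".

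**Where the controls come from.** The sections differ:
- Abstract (Methods) and Sample size calculation, General practitioner study: claims data only.
- Impact evaluation: claims and cross-insurer DMP data, the latter glossed as "triangulation in comparison to the insurer-data". The randomization section also speaks of triangulation.
- Statistical hypotheses and analyses, General practitioner study: "The control group will be calculated from insurer claims data as well as DMP-documentation data across insurers", with no division into a primary and a supporting source.

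**Subjective health.** GP quality of life is listed as primary data only. Statistical analyses, Economic evaluation, plans a difference-in-differences analysis to "analyze subjective health changes of study participants over the course of the study between intervention and control group" and does not say which of the two studies it covers.

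**The concern.** The GP study is not randomized, so its confirmatory comparison depends on both groups meeting the same entry rules. Recent periodontitis therapy is excluded because it is the route by which the intervention is meant to lower HbA1c. If some controls come from a source without that variable, recently treated patients can enter the control group but not the intervention group, on the very exposure under study.

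The protocol treats the gap in the DMP data as a limit on the secondary endpoints. It does not note that the same gap removes an eligibility variable for the primary one. With the sources described differently from section to section, the primary comparator could still be chosen after the data are seen.

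**Working it through.** **Step 1: can the rule be applied in each source?**
- Intervention patients: yes. Eligibility is checked at recruitment, and therapy use is listed as primary data.
- Claims controls: yes. Therapy use is listed as claims data.
- DMP controls: no. Therapy use is a secondary endpoint, and DMP data are said to lack these. The endpoint looks forward and the exclusion looks back 12 months, but the variable is the same, so a source without it cannot supply the look-back.

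No linkage of DMP records to claims and no proxy for past therapy is described. The comparability that is described rests on demographic characteristics. The only stated removal from the control data is of intervention practices.

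**Step 2: reproduce the planned sample size.** Inputs from Sample size calculation, General practitioner study: difference 0.2, SD 2.3, power 0.80, ICC 0.03, 10 patients per practice, control to intervention 2:1, drop-out 20%. The two-sided 5% level is from the GP hypothesis section.
- Without clustering: about 1557.5 intervention and 3115 control patients.
- Design effect: 1 + (10 − 1) × 0.03 = 1.27.
- With clustering: 1557.5 × 1.27 = 1978 and 3115 × 1.27 = 3956. The protocol states 1980 (198 practices of 10) and 3960.
- With drop-out: 1980 / 0.8 = 2475, rounded up to 248 practices or 2480 patients; 3960 / 0.8 = 4950.
- SE at 1980 and 3960: 2.3 × √[1.27 × (1/1980 + 1/3960)] = 0.0713. Power: Φ(0.2/0.0713 − 1.96) = 0.80.

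The sample size reproduces and is not in question.

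**Step 3: how large could the effect be?** The document does not give the share f of DMP controls treated in the past 12 months, nor the difference b between their T0–T1 HbA1c change and that of eligible controls. Assumed ranges: f from 2% to 20% and b from 0.2 to 0.6 points (0.6 is the therapy effect used in the sample size section), with all 3960 controls taken from DMP data.

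Shift in control mean = f × b. The power column applies only if the shift reduces the contrast: Φ((0.2 − f × b)/0.0713 − 1.96).

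| f | Ineligible of 3960 | b | Shift | Share of 0.2 | Power |
|---|---|---|---|---|---|
| 2% | 79 | 0.2 | 0.004 | 2% | 0.78 |
| 2% | 79 | 0.6 | 0.012 | 6% | 0.75 |
| 5% | 198 | 0.2 | 0.010 | 5% | 0.76 |
| 5% | 198 | 0.6 | 0.030 | 15% | 0.66 |
| 10% | 396 | 0.2 | 0.020 | 10% | 0.71 |
| 10% | 396 | 0.6 | 0.060 | 30% | 0.50 |
| 20% | 792 | 0.2 | 0.040 | 20% | 0.61 |
| 20% | 792 | 0.6 | 0.120 | 60% | 0.20 |

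The sign is unknown. Therapy whose effect came before T0 is already in the baseline value and could leave a smaller later fall, which widens the contrast. Therapy shortly before T0 could still be lowering HbA1c, which narrows it. The model adjusts for baseline HbA1c, so part of either effect would be absorbed. With claims controls only, f = 0 and the shift is 0.

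**Step 4: what does screening cost?** If the same 2% to 20% were removed from 3960 controls and not replaced, power would be 0.798 to 0.768.

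**Step 5: subjective health.** The questionnaires with the SF-36 items go to recruited patients. The dentist study recruits its control group and surveys it at T0, T1 and T2, so a controlled contrast exists there. The GP control group is calculated from records and completes no questionnaire, so it has no subjective-health values.

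**The case against.** The strongest reply is that claims data are the intended control source. The abstract and the sample size section say so, the primary model admits only covariates that claims hold, and the DMP data are introduced as a comparison with the insurer data. Comparing two sources is not merging them. On that reading the primary test is sound and the change asked for is close to what is planned. How two sources enter a model is also detail that an article may leave to the full protocol or SAP.

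Much of this stands. A reader might infer that the two groups in the confirmatory test will follow different eligibility rules; the document does not establish that. What remains is that the section defining the primary test names both sources as forming the control group, without ranking them. Followed as written, it admits controls who cannot be screened. That is a conflict between stated elements, not an omitted detail.

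Three other inferences go too far:
- **Double counting.** A cross-insurer DMP file may include the single insurer's own patients, so one might infer that people are counted twice and the standard error is too small. Pooling is never stated, and patients of other insurers would appear only once.
- **A 5% ineligible share.** One could divide the 1 million treatment cases in the Background by its 10 million people with severe periodontitis and multiply by the 50% need assumed for T2DM patients. The numerator is not restricted to severe disease, and the first two figures are not for T2DM patients. The result is not an estimate for DMP controls.
- **A failed GP quality-of-life comparison.** The difference-in-differences refers to study participants and can be computed in the dentist study. The article does not explicitly commit to it for GP patients.

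**Conclusion.** The point holds in limited form. The source of the GP primary comparator is described inconsistently, and any control drawn from DMP records cannot be screened for an exclusion that defines the primary endpoint. This follows from putting the secondary-endpoint list beside the statement on DMP content; no single sentence says it.

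Whether bias arises depends on how far DMP records enter the primary test. It is nil if they do not. If they supply every control, the assumed ranges give 2% to 60% of the target effect, in a direction the document does not settle. The upper end needs a 20% ineligible share, the full 0.6-point difference and no absorption by baseline adjustment. These figures are illustrations, not estimates.

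On subjective health, the scope of the planned contrast is left open, and only the dentist study can supply a control group for it.

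**What to change.** - In Statistical hypotheses and analyses, General practitioner study, state that the primary HbA1c test uses only insurer-claims controls with the 12-month therapy exclusion applied. Align Impact evaluation and the randomization section with this.
- State that cross-insurer DMP controls form a separate, unpooled sensitivity analysis, and acknowledge that their therapy history is unscreened. Keeping the sources apart also removes any chance of counting a person twice. If DMP controls are wanted in the primary test, describe a linkage that supplies their therapy history.
- In Statistical analyses, Economic evaluation, limit the subjective-health difference-in-differences to the dentist study and report GP subjective health as uncontrolled change over time.

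The cost is wording in the protocol and SAP. The downside is that the primary control comes from a single insurer, which the protocol itself regards as less representative; the DMP analysis examines that. Any loss of power from screening is small (Step 4).
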